## Methods

### Study design

We will conduct a parallel randomized controlled trial. This design allows us to examine pre- and post-assessments of participants randomized to the intervention (treatment group) compared to participants randomized to usual care (control group). Given our focus on individual patients, the nature of our intervention, including its reliance on training and specific tools, the risk for contamination between participants will be relatively small. Any such contamination will bias results towards the null. We considered other designs including randomizing by practice site (cluster RCT), stepped wedge and staggered enrollment trials, but did not choose these designs due to few clusters, data collection burden, and relatively short funding time frame (3 years).

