#### Patient empowerment

Our primary outcome is patient empowerment assessed using the Patient Activation Measure (PAM). We will capture related additional dimensions of empowerment including eHealth literacy (eHealth Literacy Scale eHEALS [23, 24]), patient involvement in their care (Patient Involvement in Care [25]) and, patient confidence in their health care decision making (Decision Making Self Efficacy Scale [26]).

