### Planned analysis

Following collection and cleaning of data (T0–T3), the underlying assumptions of all analyses will be checked using appropriate graphical and numerical methods [31]. Data accuracy will be investigated upon discovery of any outliers or influential data points. If an outlier is detected, we will truncate the outlier by assigning a reasonable value or replacing it using the adjacent values from the remaining data. We will try to utilize all data points in the final analysis.

The proposed study adopts a randomized repeated measures pre-test/post-test design and our analytic plan reflects this design. We will use generalized estimating equations (GEE) to obtain robust estimates and to account for the repeated measures study design and the correlated data structure of subjects nested within study site [32]. The chosen link function for the models will be appropriate for the distribution of each outcome. Unless otherwise stated, all statistical tests will be performed at the two-tailed 5 % level of significance. Likewise, 95 % confidence intervals will be constructed for estimation of effects (e.g., difference in outcomes between intervention and control groups). We will use Dunnett and Hsu’s methods to control for multiple comparisons in secondary outcomes [33]. All analyses will be performed with SAS® statistical software version 9.3 (SAS Institute, Cary NC).

We will summarize frequencies of categorical variables and means or medians for continuous and ordinal variables. Continuous variables with skewed distributions will be transformed to approximate normality. We will construct tables that display baseline characteristics for participants, overall and by (blinded) group assignment. We will compare baseline information on participants including demographic characteristics, previous computer use, and health factors. We will assess whether attrition differs across baseline characteristics or by group assignment and adjust for differences if present using multiple imputation if necessary. We will conduct intention-to-treat analyses.

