### Aim 1: Improve PLWH’s empowerment

To assess H 1.1 (Improvement in patient activation; decision making ability; and perceived knowledge, comfort, and perceived skills at finding, evaluating, and applying electronic health information to health problems), we will compare changes in patient activation (primary outcome), eHealth literacy, and decisional self-efficacy outcomes by assigned randomization group using GEE models that control for baseline scores. All models will be adjusted for any potential confounders identified by the initial analyses. We will use the same approach to assess H 1.2 (substituting Perceived Involvement in Care).

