### Aim 2: Increase PLWH’s receipt of evidence-based care

To assess H 2.1 (improvement in patient improve patient confidence in adhering to combination antiretroviral treatment (cART), self-reported adherence to cART, and HIV viral suppression), we will substitute these dependent variables in the above models. Similarly for H 2.2 (improvement in evidence-based care), we will index for evidence-based care for the dependent variable. This index will be created by passed on ratio of interventions that the patient received versus the number they were eligible for.

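### Dunnett's and Hsu's methods are named to control multiplicity in the secondary outcomes, but in a two-arm trial they give no effective error control across outcomes

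*Protocol article*

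**What the plan says.** The Study design section sets up a parallel trial with two groups: "participants randomized to the intervention (treatment group) compared to participants randomized to usual care (control group"). The effect to be estimated, under Planned analysis, is the "difference in outcomes between intervention and control groups". The same section sets the default that "all statistical tests will be performed at the two-tailed 5 % level of significance" and then gives the article's only multiplicity provision: "We will use Dunnett and Hsu’s methods to control for multiple comparisons in secondary outcomes".

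There is one primary outcome: "Our primary outcome is patient empowerment assessed using the Patient Activation Measure (PAM"). The sections on Aims 1 to 3 fit the same type of GEE model to one outcome after another. Aim 1 compares "patient activation (primary outcome), eHealth literacy, and decisional self-efficacy outcomes by assigned randomization group", and for the next hypothesis the article says "We will use the same approach to assess H 1.2 (substituting Perceived Involvement in Care"). Aim 2 continues with adherence self-efficacy and then "self-reported adherence to cART, and HIV viral suppression), we will substitute these dependent variables in the above models". It goes on to a preventive-care index, and Aim 3 to the SF-12 physical and mental components. None of these sections states a rule that links the p-values of different outcomes.

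**The concern.** Dunnett's method protects a set of contrasts in which several groups are each compared with one control. Hsu's methods concern comparison with the best of several groups, or approximate Dunnett's. Both work over the levels of one factor, within the model for one outcome. Here the treatment factor has two levels, so each outcome supplies a single contrast and there is nothing to adjust.

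The multiplicity in this trial comes mainly from the number of outcomes, and neither method acts on that. An analyst who follows the sentence as written would obtain ordinary 5% tests for every secondary treatment effect, while the plan tells the reader that multiple comparisons have been controlled. A significant secondary result could then be given more weight than it has earned.

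**Working it through.** **1. The plan's own figure.** The article states no family-wise error rate for the secondary outcomes. The one related figure is the detectable effect of 0.51 in the Power section. Its inputs are 360 enrolled, 15% drop-out, 8 sites, ICC 0.0207, significance level 0.05 and power 80%. I assume 1:1 allocation, since the ratio is not stated.

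- Analysed: 360 × 0.85 = 306; per site 306 / 8 = 38.25.
- Design effect: 1 + (38.25 − 1) × 0.0207 = 1.771.
- Effective number per arm: 153 / 1.771 = 86.4.
- Detectable effect with 8 − 2 = 6 degrees of freedom: (2.447 + 0.906) × √(2 / 86.4) = 3.353 × 0.1522 = 0.510.

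This reproduces 0.51 with an unadjusted two-sided 0.05, so the design figure contains no allowance for multiplicity.

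**2. What Dunnett does with one contrast.** In a simulated example with 153 per arm, Dunnett's p-value was 0.0278 and the ordinary t-test gave 0.0278. The adjustment is nil.

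**3. Number of secondary outcomes.** This count is mine, from Table 4 and the sections on Aims 1 to 3:

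- eHealth literacy, decision self-efficacy, involvement in care (3);
- adherence self-efficacy, past-week adherence (2);
- viral load level, undetectable viral load (2);
- preventive-care index (1);
- SF-12 physical and SF-12 mental (2).

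The total is 10. It is 9 without viral load level, which appears as a measure in Table 4 while the Aim 2 analysis names suppression. It is 8 if the SF-12 is also counted once, and 11 if clinician communication is added.

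**4. Family-wise error with no adjustment across outcomes.** With all nulls true and independent tests, the chance of at least one false positive is 1 − 0.95^k:

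| k | chance of at least one false positive |
|---|---|
| 8 | 33.7% |
| 9 | 37.0% |
| 10 | 40.1% |
| 11 | 43.1% |

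For k = 10 with an assumed common correlation (simulation of equicorrelated normal statistics, 400,000 replicates):

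| correlation | unadjusted 5% | each test at 0.05 / 10 = 0.005 |
|---|---|---|
| 0.3 | 35.3% | 4.6% |
| 0.5 | 28.7% | 3.8% |
| 0.8 | 17.1% | 2.3% |

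**5. What real control costs in power.** Holm's strictest step for 10 outcomes is 0.005. By the method of step 1, the detectable effect there is (4.317 + 0.906) × 0.1522 = 0.79, against 0.51. With normal quantiles and the same design effect it goes from 0.43 to 0.56. Later Holm steps are less strict.

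**The case against.** The strongest reply is that the two methods may have been meant for comparisons within an outcome. Planned analysis describes a repeated-measures design, most scales are collected at T0, T1 and T2, and race has four categories that enter the H 4.2 interactions. Comparing two later visits with baseline is a several-against-one structure in which Dunnett does adjust. A reader might infer from the two-arm design that the methods adjust nothing anywhere in this trial. The article does not support that, because such within-outcome use is possible. It would still leave error across outcomes uncontrolled, so the narrower statement stands.

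A second reply is that the article never promises a 5% family-wise rate over all secondary outcomes and never lists a family. That is correct. The figures above show what goes uncontrolled; they are not a breach of a stated number. Nor does the article say how secondary results will be reported, so one cannot assert that they will be presented as adjusted.

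Third, independence is the least plausible case. Viral load level and suppression come from the same measurement, and several of the scales overlap in construct. This lowers the figure, but even at a correlation of 0.8 it is more than three times 5%.

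Finally, many trials leave secondary outcomes unadjusted, and a separate analysis plan may handle the matter. Leaving them unadjusted is legitimate when declared; this article instead claims control by a named method. If another document says something different, the two need to be reconciled.

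**Conclusion.** The point holds as a mismatch between method and task. The named methods leave each secondary treatment-versus-control p-value unchanged, and nothing else in the article controls error across outcomes. The chance of at least one false positive is about 34% to 43% for 8 to 11 independent outcomes, and about 17% to 35% for 10 outcomes at correlations from 0.8 down to 0.3. These figures rest on a derived count, assumed correlations and all secondary nulls being true.

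A reader might go further and conclude that the trial's main inference is compromised. The article does not support that: PAM is a single primary outcome, its test does not depend on this sentence, and nothing makes the trial's conclusion hang on a secondary outcome. The point is therefore one that should be fixed, not one that must be fixed before the trial can be relied on.

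**What to change.** Replace the sentence in Planned analysis with wording such as: *PAM is tested alone at two-sided 5%. The treatment-versus-control p-values for the listed secondary outcomes are adjusted with the Holm (or Hochberg) procedure as one family; unadjusted 95% confidence intervals are also given.* List the family once, settling whether viral load level and clinician communication belong to it and whether the SF-12 counts once or twice. At minimum, drop the claim of control and label the secondary outcomes as supportive, with unadjusted intervals. If Dunnett's or Hsu's method is wanted for visits or categories, say so separately.

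The change needs no new data and no change of design, and it should be made before anyone sees results by arm. The cost is power for secondary claims: under Holm with 10 outcomes, the smallest p-value must be at or below 0.005 before any can be claimed (Hochberg can be less strict). The Power section should then state that 0.51 holds at an unadjusted 0.05 only. Four of the five measures in Table 6 are secondary, and at the strictest Holm step the detectable effect for them is about 0.79 by the same method.

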Every effort will be made to facilitate and encourage participants’ completion of all surveys. In the event that missing data occur, we will attempt to contact participants and obtain the data or to find out why the surveys or items are missing. The reasons for missing data will be documented and the mechanism for missing data will be examined [34]. If needed, data will be imputed and a weighted generalized estimating equations (WGEE) model will be applied using the inverse probability of missingness as the sample weight [35]. Sensitivity analyses will be performed to determine the impact of key assumptions.

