### Power

The number of participants included in the intervention group and the usual care groups is based upon a series of power analyses. For H 1.1 – H 3.1, we estimated detectable difference using the method described by Donner and Klar, [36] using 8 study sites total, a significance level of 0.05, and a minimum power of 80 %. The intra-cluster correlation (ICC = 0.0207) was estimated from our pilot data and is consistent with other studies [37]. We plan to enroll 360 participants to allow for attrition and assume a 15 % drop-out rate. Thus, we will be able to detect an effect size of 0.51 for each of the measures in Table 6. For H 4.1 and H 4.2, we ran Monte Carlo simulations to determine that we will have a minimum of 80 % power for the interactions [38].

**Table 6 Tab6:** Change in empowerment dimensions (effect size) by participant education, activation or eHealth literacy

Empowerment dimension	<High school	High school	>High school	Low activation	High activation	Low eHealth literacy	High eHealth literacy
HIV adherence self-efficacy	0.15	−0.64	−0.19	0.18	−0.38	−0.02	−0.05
eHealth literacy	0.85	0.35	0.61	0.98	0.18	0.94	0.35
Perceived Involvement in Care	0.57	0.37	0.24	0.61	0.11	0.48	0.26
Decision self-efficacy	0.81	0.23	0.34	0.86	0.16	0.48	0.52
Patient Activation	0.50	−0.85	0.24	0.52	−0.155	0.32	0.11

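### The weight stated for the weighted GEE is inverted: it should be the inverse probability of being observed, not of being missing

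*Protocol article*

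**What the plan says.** The main models compare the arms "using GEE models that control for baseline scores" (Aim 1), and Aims 2 and 3 use the same approach. For missing data, Planned analysis says: "If needed, data will be imputed and a weighted generalized estimating equations (WGEE) model will be applied". The weight is fixed in the same sentence: "weighted generalized estimating equations (WGEE) model will be applied using the inverse probability of missingness as the sample weight". An earlier paragraph of the same section says that, where attrition differs by baseline characteristics or by arm, the team will "adjust for differences if present using multiple imputation if necessary". No other part of the article defines the weight differently. On the amount of missing data, Power gives one overall figure: "We plan to enroll 360 participants to allow for attrition and assume a 15 % drop-out rate".

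**The concern.** Inverse-probability weighting lets each observed participant stand in for similar participants who were lost. That needs larger weights for observed people whose chance of being observed was low. The inverse of the missingness probability does the opposite: someone with a 5% chance of being missing gets weight 1/0.05 = 20, and someone with a 25% chance gets 1/0.25 = 4.

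The direction matters in this trial. Background says that poor and minority patients miss more office visits, and the T2 survey is timed to an HIV visit, so unequal missingness is plausible. H 4.1 expects the greatest improvement in those with the lowest baseline activation. If such participants are also lost more often, the stated weights play down the group in which most benefit is expected. Code with this weight would run without error, so the output would not reveal the mistake.

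**Working it through.** **Inputs.** From the article: 15% overall dropout and 360 enrolled (Power); baseline-adjusted GEE (Aim 1); pilot changes in Patient Activation of 0.52 (low activation) and −0.155 (high activation) (Table 6). Assumed, because the article does not give them: how dropout divides between kinds of participant, and how the effect varies with baseline.

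**The plan's own figure.** The article gives no number for the weights. The nearest figure is the detectable effect of 0.51, and it reproduces: 360 × 0.85 = 306 analysable, 153 per arm (1:1 assumed), 38.25 per site, design effect 1 + 37.25 × 0.0207 = 1.771. With 6 degrees of freedom, (t₀.₉₇₅ + t₀.₈₀) × √(2 × 1.771/153) = 0.510. It does not depend on the weights.

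**Step 1: what each weight does.** Let p be the probability of being missing. A participant is observed with probability 1 − p, so the expected contribution is (1 − p) × weight.
- Weight 1/(1 − p): contribution 1 for everyone, so the randomised sample is restored.
- Weight 1/p: contribution (1 − p)/p, which rises steeply as p falls.

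**Step 2: two equal strata, 15% missing overall.** With 25% and 5% missingness, the share of the total carried by the high-dropout half is:
- unweighted: 0.375/(0.375 + 0.475) = 44%
- 1/(1 − p): 0.5/(0.5 + 0.5) = 50%
- 1/p: 0.5 × 0.75 × 4 = 1.5 against 0.5 × 0.95 × 20 = 9.5, so 1.5/11 = 14%

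If the high-dropout half is the low-activation half, and the Table 6 changes are used only to show scale, the true mean change is (0.52 − 0.155)/2 = 0.1825.

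| Missingness, low/high activation | Unweighted | 1/(1 − p) | 1/p as written |
|---|---|---|---|
| 15% / 15% | 0.1825 | 0.1825 | 0.1825 |
| 20% / 10% | 0.163 | 0.1825 | 0.053 |
| 25% / 5% | 0.143 | 0.1825 | −0.063 |

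**Step 3: baseline-adjusted arm contrast.** Let x be a standardised baseline score, included in the outcome model. Outcome = (0.30 − 0.2x) × arm + 0.6x + 0.8 × noise, with logit p = −2 − 0.8x in both arms (about 14% missing). The average effect is 0.30.
- Unweighted: 0.28.
- 1/(1 − p): 0.30.
- 1/p: (1 − p)/p = exp(2 + 0.8x), which moves the weighted mean of x from 0 to 0.8, so the estimate is 0.30 − 0.2 × 0.8 = 0.14.

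A separate simulation (360 participants, 2,000 runs, 15% dropout, true effect 0.25, effect falling by 0.25 per SD of baseline, baseline in the model) gave, in the same order, 0.229, 0.246 and 0.125 when the log-odds of dropout changed by 0.5 per SD. At 1.0 per SD the results were 0.217, 0.248 and 0.016.

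**Step 4: where there is no bias.** With constant p the three weightings agree (first row of the table). With a homogeneous effect of 0.30 and x in the outcome model, all three give about 0.30, even when dropout depends on x more strongly in one arm. The bias also cancelled in a baseline-adjusted run with a varying effect where dropout depended on x in opposite directions in the two arms (0.248 against 0.25).

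**Step 5: precision.** Effective sample size is (Σw)²/Σw², as a share of completers. In the 25%/5% case with weights as written, Σw = 11 and Σw² = 0.375 × 16 + 0.475 × 400 = 196. So 121/196 = 0.617, and 0.617/0.85 = 73%. With correct weights it is 99%. Across the assumed dropout models the range was about 47% to 87% as written, against 98% to 100% with correct weights.

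**The case against.** The best reply is that this is a slip of the pen. Weighted GEE is a standard named method, and a statistician would probably code it correctly. That may be so, but the published rule is wrong as it stands and nothing else in the article corrects it.

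The second reply is that the reach is limited. The default GEE is unweighted and unaffected, and the models adjust for baseline scores and for confounders found in the initial analyses. This stands, and it removes the bias when the driver of dropout is in the model and the effect is homogeneous. It does not do so in general when the effect varies with that driver.

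Four stronger readings are tempting, and the article does not support them:
- **The sign of the result would reverse.** If the driver is left out of the outcome model, its coefficient is 0.6, and the dropout slopes are 0.3 (treated) and 1.0 (control), the stated weights give 0.30 + 0.6 × (0.3 − 1.0) = −0.12. Once the driver is in the model the result returns to 0.30. This is one steep scenario and not a forecast. The negative entry in the Step 2 table is likewise no forecast, because it rests on uncontrolled pilot changes.
- **Unweighted GEE is valid only if data are missing completely at random.** It also holds when missingness depends only on arm and on covariates in a correctly specified mean model.
- **Imputing and weighting contradict each other.** The article distinguishes missing surveys from missing items. Imputing items and weighting for lost surveys is coherent.
- **The if-needed trigger, the weight-model covariates and the choice of main method are defects.** A condensed article commonly leaves these to the full protocol or analysis plan.

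**Conclusion.** The weight is stated the wrong way round and should be corrected. Taken literally it down-weights the observed participants who best represent the dropouts: 14% of the weight instead of 50% in the 25%/5% case.

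The consequence is conditional and confined to the if-needed weighted analysis. Where missingness varies but the no-bias conditions hold, the cost is precision. Where the effect varies with the driver of dropout, the stated weights can be further from the truth than no weighting: in Step 3 the error is 0.16 (0.30 − 0.14) against 0.02 unweighted (0.30 − 0.28). These sizes rest on assumed dropout patterns and effect heterogeneity. That the weight is inverted rests on no assumption.

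**What to change.** In the missing-data paragraph of Planned analysis, replace the description of the weight with: *the inverse of the estimated probability that the outcome is observed, given arm and observed history*. Check that any analysis plan and program code use the same definition. The cost is one phrase. Sample size, data collection and the default GEE do not change.

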### Aim 1: Improve PLWH’s empowerment

To assess H 1.1 (Improvement in patient activation; decision making ability; and perceived knowledge, comfort, and perceived skills at finding, evaluating, and applying electronic health information to health problems), we will compare changes in patient activation (primary outcome), eHealth literacy, and decisional self-efficacy outcomes by assigned randomization group using GEE models that control for baseline scores. All models will be adjusted for any potential confounders identified by the initial analyses. We will use the same approach to assess H 1.2 (substituting Perceived Involvement in Care).

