### Procedures for randomization and allocation

Sequential identification (ID) numbers will be generated by our study biostatistician using computer generated random numbers stratified by site (Rochester or NYC) to minimize potential site variation between groups. Assignments will be concealed in sealed opaque, envelopes that contain the group assignment. Following confirmation of the participant’s eligibility, informed consent, and completion of the baseline assessment (T0), the RA will open the envelope and notify the participant whether they have been assigned to the intervention or usual care group.

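### The primary model takes its covariates from the trial's own baseline comparisons; a set fixed in advance would be better calibrated and modestly more precise

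*Protocol article*

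**What the plan says.** Under Aim 1, the protocol article compares change in PAM (the primary outcome) and the related empowerment scores between arms "using GEE models that control for baseline scores". The next sentence reads: "All models will be adjusted for any potential confounders identified by the initial analyses". It covers every model, including the primary one, and Aims 2 and 3 reuse the same models.

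Planned analysis shows what the initial analyses are. The first is a baseline comparison: "We will compare baseline information on participants including demographic characteristics, previous computer use, and health factors". The second is a check on whether attrition differs by baseline characteristic or by arm, with the instruction to "adjust for differences if present using multiple imputation if necessary". Baseline tables are to be laid out with arm labels masked. The section opens by placing the analysis after the T0 to T3 data have been collected and cleaned.

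Randomisation is of individual patients, stratified by region (Rochester or NYC), with concealed allocation (Procedures for randomization and allocation).

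**The concern.** The text commits the primary model to covariates that the trial's own data will pick. Confounding of arm by baseline characteristics is a problem of observational studies. Where individuals are randomised, a difference between arms at T0 is a chance event, and its size says nothing about whether the variable predicts PAM. A rule that reacts to such differences has two effects.

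- It includes prognostic variables only in the samples where they happen to be unbalanced. This removes some bad draws, so the true variability of the estimate falls. The reported standard error does not know this and comes out too large.
- In the other samples the prognostic variables are left out, and the precision they offer is lost.

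At stake are the width of the primary confidence interval and how firmly the primary model is settled before results are seen.

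**Working it through.** **Inputs from the protocol article.** 360 enrolled, 15% dropout, 8 sites, ICC 0.0207, minimum power 80% (Power); two-sided 5% tests (Planned analysis); baseline score always in the model (Aim 1).

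**Assumptions, not in the document.** 1:1 allocation; 8 independent normal candidate covariates, 4 of them prognostic; partial R² (share of the variance left after the baseline score) of 0.02, 0.10 or 0.20; selection by a baseline test at p<0.05 or p<0.20.

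**Step 1: the plan's own figure.**
- Completers: 360 × 0.85 = 306, or 153 per arm and 306/8 = 38.25 per site.
- Design effect: 1 + 37.25 × 0.0207 = 1.771.
- With t quantiles on 8 − 2 = 6 df: (2.447 + 0.906) × √(2 × 1.771/153) = 0.510.

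The stated 0.51 is reproduced. No covariate enters the formula, so the adjustment rule does not affect it.

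**Step 2: how often chance supplies a covariate.** With k independent variables tested at 5%, the probability of at least one imbalance is 1 − 0.95^k: 23% for k = 5, 34% for k = 8, 54% for k = 15.

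**Step 3: reference effect.** Without a design effect, (1.960 + 0.842) × √(2/153) = 0.320. Rules are compared at 0.32, measured in SDs remaining after the baseline score, because power there is near 80% and differences show.

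**Step 4: what a fixed set can gain.** The standard error shrinks by √(1 − R²): a factor of 0.949 at 0.10 and 0.894 at 0.20, or about 5% and 11%. In patients this is worth 306/0.90 = 340 and 306/0.80 = about 382 completers.

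**Step 5: simulation.** ANCOVA with 306 patients and the baseline score in every model, 40,000 replicates per setting.

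| Partial R² | Rule | Type I error | Reported SE / true SE | Power at 0.32 |
|---|---|---|---|---|
| 0.10 | all 8 fixed | 4.9% | 1.00 | 82.5% |
| 0.10 | imbalance p<0.05 | 4.8% | 1.01 | 79.7% |
| 0.10 | imbalance p<0.20 | 4.4% | 1.02 | 80.1% |
| 0.20 | all 8 fixed | 5.1% | 1.00 | 86.8% |
| 0.20 | imbalance p<0.05 | 4.5% | 1.02 | 80.3% |
| 0.20 | imbalance p<0.20 | 4.0% | 1.05 | 81.6% |

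Power lost against the fixed set: 82.5 − 79.7 = 2.8 and 82.5 − 80.1 = 2.4 points at 0.10; 86.8 − 80.3 = 6.5 and 86.8 − 81.6 = 5.2 points at 0.20. Coverage of the 95% interval under imbalance selection is 95.3-96.1%. Monte Carlo standard error is √(0.05 × 0.95/40,000) = 0.1 point for type I error and about 0.2 point for power, so 4.8% against 4.9% is noise while the power gaps are not.

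**Step 6: where the effect disappears** (6,000 replicates, Monte Carlo error about 0.5 point of power). At partial R² 0.02 the rules differ by under 1 point. If covariates are chosen by association with the outcome, coverage is nominal and power is 82.0% and 86.5% at 0.10 and 0.20, almost all of the fixed-set value.

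The simulation has no site correlation and no repeated measures.

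**The case against.** **A covariate list belongs in the analysis plan, which is not shown.** This is correct as far as a missing list, a missing threshold or an unnamed stratum term goes, and none of these is the point here. The article does more than stay silent: it states a rule that draws the covariates from the data, and a later fixed list would have to override it. On location, GEE already allows for clustering within study site. That is not a fixed term for the randomisation stratum, but it means location is not ignored.

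**The strongest predictor is already in the model.** This stands. Only precision beyond the baseline score is at issue, and the simulation is set up that way.

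**The text does not say that selection is by imbalance.** This stands as a limit. The baseline comparison is the reading that Planned analysis best supports, but selection by association with the outcome is possible and would do little harm.

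**Randomisation does not protect against differential dropout.** This also stands. A reader might infer that there can be nothing to adjust for. The attrition check and the expected 15% dropout show that this is too strong, because adjusting for predictors of dropout can be legitimate.

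**A reader might infer that the rule inflates false positives.** The document does not support that. The stated sequence is baseline comparisons with arms masked, and under that sequence the test errs on the cautious side. If covariates were chosen after seeing treatment p-values, simulated type I error would be 6.6-10.0% over partial R² 0.02-0.20. The article does not describe such conduct, though its wording does not rule it out: nothing says the set is closed before treatment estimates are seen.

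**Conclusion.** The point holds in a limited form. Choosing covariates for the primary PAM model from baseline comparisons is a poor rule in an individually randomised trial. On that reading the cost is a slightly conservative test and a modest loss of precision. The size depends on how much the extra covariates predict beyond the baseline score, which the document does not give: from nothing measurable at partial R² 0.02 to 5-7 points of power at 0.20.

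It would be wrong to infer that the sample size fails. At the protocol's own 0.51, an individually randomised comparison of 153 per arm without a design effect has 99.4% power before any further covariate is added. The loss is in interval width and in how tightly the primary model is pinned down. The change is worth making, but the trial's validity does not hang on it.

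**What to change.** For the primary model, replace the confounder sentence under Aim 1 with a covariate set fixed before unblinding and kept whatever imbalance is observed:

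- the baseline score, as already planned;
- the randomisation stratum (Rochester or NYC);
- a short list of T0 variables that the sponsor expects to predict PAM.

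Report any adjustment prompted by baseline imbalance or by the attrition check as a labelled sensitivity analysis.

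The cost is wording only. Table 4 already has demographics, computer experience, health history and the scales collected at T0, so no new data, visits or patients are needed.
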